## Abstract

**Background:**

Prostate cancer is the most common male cancer in the Western world however there is ongoing debate about the optimal treatment strategy for localised disease. While surgery remains the most commonly received treatment for localised disease in Australia more recently a robotic approach has emerged as an alternative to open and laparoscopic surgery. However, high level data is not yet available to support this as a superior approach or to guide treatment decision making between the alternatives. This paper presents the design of a randomised trial of Robotic and Open Prostatectomy for men newly diagnosed with localised prostate cancer that seeks to answer this question.

**Methods/design:**

200 men per treatment arm (400 men in total) are being recruited after diagnosis and before treatment through a major public hospital outpatient clinic and randomised to 1) Robotic Prostatectomy or 2) Open Prostatectomy. All robotic prostatectomies are being performed by one surgeon and all open prostatectomies are being performed by one other surgeon. Outcomes are being measured pre-operatively and at 6 weeks and 3, 6, 12 and 24 months post-surgery. Oncological outcomes are being related to positive surgical margins, biochemical recurrence +/− the need for further treatment. Non-oncological outcome measures include: pain, physical and mental functioning, fatigue, summary (preference-based utility scores) and domain-specific QoL (urinary incontinence, bowel function and erectile function), cancer specific distress, psychological distress, decision-related distress and time to return to usual activities. Cost modelling of each approach, as well as full economic appraisal, is also being undertaken.

**Discussion:**

The study will provide recommendations about the relative benefits of Robotic and Open Prostatectomy to support informed patient decision making about treatment for localised prostate cancer; and to assist in treatment services planning for this patient group.

**Trial registration:**

ACTRN12611000661976

## Background

Because of an absence of objective information from randomised studies, it is advised that men diagnosed with localised prostate cancer (PCa) are offered three broad treatment approaches that include surgery or radical prostatectomy (RP), irradiation of the prostate, or observation in the form of active surveillance or watchful waiting [1]. In practice, however, multiple options are often presented that arise not only through treating clinicians, but from family, friends, the media, and self-help programs [2]. The option list can then include an array such as open, laparoscopic & robotic RP, external beam radiation, high and low-dose brachytherapy, high frequency focussed ultrasound, a variety of alternative therapies and monitoring. For each approach, the newly diagnosed man must consider costs and benefits from a survival and quality of life (QoL) point of view, financial costs and relative availabilities.

In this decision context, high quality evidence about the expected outcomes of each approach is essential however, problematic for robotic procedures, this information is lacking. Specifically, data on QoL outcomes comparing robotic procedures with open RP are typically from case series from single centres [3-6], with, to our knowledge, only one other randomised controlled trial being undertaken, comparing open, laparoscopic and robotic prostatectomy (the LopeRA study) which is experiencing difficulty recruiting patients [7,8]. This paucity of high-quality information leaves men with localised prostate cancer, and their physicians, in the difficult position of trying to make a treatment decision without high quality evidence. Moreover there is evidence that once robotic surgery becomes available, consumer demand drives up its usage, with one study reporting that during the course of a case series to compare robotics with other approaches, at the study completion more than 94% of men had chosen robotic surgery [5]. This means there are also health services planning and delivery issues that arise from this evidence gap.

To date, case series suggest varied outcomes when comparing robotic with open RP. Some suggest that patients who undergo robotic surgery have less post-operative narcotic use, shorter hospital stays [6] and better short term urinary and sexual function [3,5]. Other studies have found no clear differences in functional outcomes with regards to potency, continence [9], pain and recovery [10]. Finally, the methodological issues that ensue from selection bias in case series and the use of non-standard reporting methods make much of this data difficult to interpret [4,11].

The present study will address this knowledge gap by completing the first randomised trial with men with localised prostate cancer comparing robotic with open RP and assessing QoL and psychosocial outcomes using reliable and previously validated measures of pain, physical and mental functioning, fatigue, summary (preference-based utility scores) and domain-specific QoL (urinary incontinence, bowel function and erectile function), cancer specific distress, psychological distress, decision-related distress and time to return to usual activities. Outcomes are being measured pre-operatively and at 6 weeks and 3, 6, 9, 12, 18 and 24 months post-surgery. Co-morbidity is being considered as a critical issue in deciding who may ultimately benefit from treatment. An economic evaluation is addressing the question of whether open or robotic RP is better ‘value-for-money’, having regard to their comparative costs and outcomes [12-14]. The economic model is integrating the surgical/clinical indices and QoL data from the trial, with the resource costs of the inputs necessary to implement both intervention arms.

## Methods/design

### Study aims and hypotheses

The study aims are to assess the quality of life effects of robotic surgery compared with open prostatectomy; determine the economic costs of robotic versus open prostatectomy with regards to both health sector costs and direct and indirect cost to patients; evaluate life expectancy profiles of patients receiving both forms of prostatectomy.

We hypothesise that:

1. There will be no difference between the two groups in terms of surgical and clinical indices of oncological outcome.

2. Patients randomised to robotic prostatectomy will have improved short term (3 months postoperative) quality of life outcomes compared with those randomised to open prostatectomy with regards to pain, physical functioning, fatigue; summary (AQoL-8D and SF36) and domain specific quality of life (urinary incontinence, bowel function and erectile function), time to return to usual activities.

3. Patients randomised to open prostatectomy will have comparable medium (6–12 months) and long term (24 months) quality of life outcomes compared with those randomised to robotic prostatectomy with regards to pain, physical functioning, fatigue; summary (AQoL-8D and SF36) and domain specific quality of life (urinary incontinence, bowel function and erectile function).

4. There will be no difference between the two groups with regards to psychological distress, cancer specific distress and decision-related distress.

5. There will be a short-term and overall cost advantage for open prostatectomy.

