### Health related quality of life

Health related quality of life is being assessed with the SF-36 that is the most widely used QOL measure in the world with norms for the Australian general population available. The SF-36 [25] contains a mental health and physical health summary scale suitable to measure the impact of the intervention on patients’ wellbeing. As well, the Assessment of Quality of Life – 8D (AQoL-8D) will be administered [26]. The AQoL-8D is a 35-item scale assessing quality of life on eight dimensions including: independent living, relationships, mental health, self worth, happiness, coping, pain, and sensory perception. The AQoL-8D is the primary outcome instrument for the economic appraisal, has excellent psychometric properties and has been used in over 80 trials in Australia.

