### Statistical analyses

The study design involves a two group Randomised trial with five assessment points. As the hypotheses involve comparisons of the rate of change with which men in the treatment versus control groups will achieve optimal physical and psychological QoL, the appropriate analysis is a two level multilevel model (with Level 2 = men and Level 1 = Assessment points). These analyses will be adjusted to account for equivalence testing procedures where appropriate with respect to the hypotheses. Although power models are not articulated for multilevel analysis as clearly as they are for ordinary linear modelling, the Optimal Design software of Raudenbush [29] and the simulation work of Jo [30] suggest appropriate sample sizes. Assuming that at least 70% of the men in each group will remain in the study (this is highly conservative as we have previously demonstrated only a 10% attrition rate in QoL studies with men with PCa) and assuming further moderate effect size of d = 0.5 and alpha at .05, a total sample size if 400 (i.e. 200 per group) would result in over 90% power.

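### Hypothesis 2 claims a 3-month robotic benefit on nine unranked outcomes, and the alpha, effect size and power are tied to none of them

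*Protocol article*

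**What the plan says.** In the protocol article, under Study aims and hypotheses, Hypothesis 2 states: "Patients randomised to robotic prostatectomy will have improved short term (3 months postoperative) quality of life outcomes". The outcomes it covers are introduced by "with regards to pain, physical functioning, fatigue; summary (AQoL-8D and SF36) and domain specific quality of life (urinary incontinence, bowel function and erectile function"), and the list ends with "domain specific quality of life (urinary incontinence, bowel function and erectile function), time to return to usual activities". Counted out, they are (1) pain, (2) physical functioning, (3) fatigue, (4) AQoL-8D, (5) SF-36, (6) urinary incontinence, (7) bowel function, (8) erectile function and (9) return to usual activities. The section Health related quality of life says that the SF-36 "contains a mental health and physical health summary scale", so the fifth item may be two scores and the list ten.

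This is the only superiority hypothesis on patient outcomes. Hypotheses 1 and 4 expect no difference, Hypothesis 3 expects comparability, and Hypothesis 5 concerns cost.

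The text shown calls one measure primary, and only for a different purpose: "The AQoL-8D is the primary outcome instrument for the economic appraisal". The section Economic appraisal repeats that role.

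Statistical analyses sizes the trial at 200 men per arm, "assuming further moderate effect size of d = 0.5 and alpha at .05", for power of more than 90%. It does not say whether alpha is one- or two-sided, and it names no outcome for the effect size or the power.

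**The concern.** Choosing the comparison that a trial is sized to answer belongs in the protocol. Here the size is justified by one generic effect, while the superiority claim spreads over nine outcomes of equal standing. The text does not say whether one, some or all of them must favour robotic surgery for Hypothesis 2 to be supported. It therefore cannot be read off in advance which result would confirm the hypothesis, or which comparison has the stated power.

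If a single favourable outcome is enough, the chance of a spurious claim is well above the nominal level. The article says that its results are meant to inform men's treatment choices and service planning, and its Background notes that demand already raises robotic use. One domain that differs by chance could then be presented as randomised evidence of benefit.

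**Working it through.** **Inputs.** From the article: 200 men per arm, d = 0.5, alpha .05, power above 90%, and nine or ten outcomes. On retention: "Assuming that at least 70% of the men in each group will remain in the study", so 0.70 × 200 = 140 per arm. The article also reports that "we have previously demonstrated only a 10% attrition rate in QoL studies with men with PCa", which would leave 0.90 × 200 = 180 per arm. Assumed here, because the article does not give them: two-sided alpha, and equal correlations between outcomes of 0, 0.5 or 0.7.

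**1. The plan's own power.** For a two-sample t test with 140 per arm, the noncentrality is d × √(n/2) = 0.5 × √70 = 4.18 on 278 degrees of freedom. The two-sided 5% critical value is 1.97, and power is 98.6%. The stated figure of more than 90% is reproduced, with room to spare.

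**2. Chance of a false claim with no true effect, if any one outcome suffices.** At two-sided .05, each test has a 2.5% chance of wrongly favouring robotic surgery.
- Nine independent outcomes, robotic direction: 1 − 0.975⁹ = 20.4%.
- Nine independent outcomes, either direction: 1 − 0.95⁹ = 37.0%.

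For correlated outcomes, equicorrelated normal test statistics were simulated (1,000,000 draws):

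| Outcomes | Correlation | False robotic benefit | Any false difference |
|---|---|---|---|
| 9 | 0 | 20% | 37% |
| 9 | 0.5 | 14% (13.5%) | 27% |
| 9 | 0.7 | 10% | 20% |
| 10 | 0 | 22% | 40% |
| 10 | 0.5 | 14% | 29% |
| 10 | 0.7 | 11% | 21% |

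Some positive correlation is likely, because the AQoL-8D itself includes a pain dimension. With nine outcomes, the directional error is about four times (10.1/2.5) to eight times (20.4/2.5) the nominal 2.5%. If alpha .05 were meant one-sided, the false robotic benefit would be 37%, 23% and 18% at correlations 0, 0.5 and 0.7.

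**3. Cost of full control.** Bonferroni sets the per-outcome level at .05/9 = .0056 or .05/10 = .005. Holm is never less powerful than Bonferroni, so these power figures are lower bounds for Holm. Noncentral t, two-sided:

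| Per arm | d | alpha .05 | .05/9 | .05/10 |
|---|---|---|---|---|
| 140 | 0.5 | 98.6% | 91.6% | 91.1% |
| 180 | 0.5 | 99.7% | 97.4% | 97.2% |
| 140 | 0.4 | 92% | 71% | 70% |

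By the normal approximation, 90% power at .05/9 and d = 0.5 needs 132 men per arm, or 132/0.70 = 189 recruited, which is below 200. For ten outcomes it needs 134, or 192 recruited.

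**The case against.** The strongest objection is that multiplicity rules are commonly left to the analysis plan, which is not shown, and that a journal article is condensed. That is right as far as it goes: the absence of an adjustment rule is not the point here. What stands is what the article itself fixes, namely a nine-part superiority claim and a sample-size statement attached to none of the nine. Even so, the absence of a ranking can be checked only against the text shown, from which some passages were removed.

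Second, the article nowhere says that one significant outcome would be enough. This also stands. If all nine had to succeed, there would be no inflation, so the error rates above are conditional on a rule that the text neither states nor excludes.

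Third, a reader might take 20–37% as the chance of a false robotic benefit. The documents do not support that. At two-sided .05 this is the range for any false difference in either direction, while Hypothesis 2 is directional, with a range of about 10–20%. The 37% would apply to robotic benefit only with one-sided .05 and independent outcomes, and the article states no sidedness. Nor can a positive result be called likely by chance: every figure above is about 40% or less.

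Fourth, the power figures are two-sample approximations at one time point. The planned analysis is a two-level model of change over time, for which the article gives no variance components. That limitation stands.

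**Conclusion.** The concern holds in this form. Hypothesis 2 makes nine or ten outcomes co-equal, and the text shown does not say which of them the alpha, d and power refer to. If each is tested at two-sided .05 and any one may carry the claim, the chance of a false robotic benefit with nine outcomes is about 20% under independence, and about 14% or 10% at correlations of 0.5 or 0.7, against 2.5% nominal. The correlations and the any-one rule are assumptions. That the outcomes are unranked and the power statement unattached is read directly from the text and needs neither.

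The planned size can carry full control at the plan's own d = 0.5 and 70% retention. It would be going too far to say so for smaller effects, or for return to usual activities if that is analysed as a time to event.

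**What to change.** Amend the hypotheses and Statistical analyses sections in one of two ways.

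- **Single primary outcome.** Name one 3-month outcome, with its instrument and score, as primary for Hypothesis 2, and tie d, alpha and power to it.
- **Controlled family.** Fix one instrument and score for each construct, then treat the nine (or ten) 3-month comparisons as one family at two-sided 5% by Holm. Claim benefit only for outcomes that pass. The instruments must be settled first: sexual function is measured by both EPIC and the five-domain IIEF, and the SF-36 has two summary scales.

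Either way, state that alpha is two-sided, and report the remaining comparisons with confidence intervals and no superiority claim.

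The cost is about one paragraph and no extra men. A single primary outcome keeps 98.6% power at d = 0.5 with 140 per arm, but limits the superiority claim to one domain. The family keeps at least 91.6% per outcome for nine (91.1% for ten). Its real price is at smaller effects: at d = 0.4, Bonferroni power for nine is about 71%, against 92% unadjusted. The restated power should say that it is a two-sample approximation and give separate support for return to usual activities if that is analysed as a time to event.

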### Study integrity

Ethical approval has been obtained from the RBWH Human Research Ethics Committee. The study design is guided by the CONSORT statement [15]. All men provide written informed consent. Assessments are by self-report pen and paper measures with project staff tracking assessments. Randomisation occurs in blocks of 10, with each condition randomly generated 5 times within each block to ensure an unpredictable allocation sequence with equal numbers of men in each group at the completion of each block. This sequence is undertaken using a computerised database independent from the clinical team and research staff. Stratification occurs by age group (40–49 yrs, 50–59 yrs, 60-69 yrs); and IPSS score (0–7, 8–19, 20–35). Following randomisation, patients are telephoned the same day to be notified of their designated surgical procedure and posted an information booklet outlining expectations for their scheduled operation. Following this, patients are placed on the surgical waiting list at the RBWH and scheduled for surgery as per standard hospital procedures. Biopsy slides are reviewed pre-operatively by staff pathologists [name], [name] or [name] all of whom have recognised expertise in uropathology.

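### One fixed, disclosed block size of 10 with forced 5:5 balance does not make the allocation sequence unpredictable, and leaves a conditional risk of selection bias

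*Protocol article*

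**What the plan says.** The Study integrity section of the protocol article gives the rule and its purpose together: "Randomisation occurs in blocks of 10, with each condition randomly generated 5 times within each block to ensure an unpredictable allocation sequence". The same sentence names a second purpose, that the two arms are level in size whenever a block ends. The section adds a safeguard: "This sequence is undertaken using a computerised database independent from the clinical team and research staff". Allocation is stratified by three age bands and three IPSS bands, which makes nine cells. That the blocks run within these cells is implied, not stated.

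Three other statements bear on who can see past allocations:

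- After randomisation, "patients are telephoned the same day to be notified of their designated surgical procedure" (Study integrity).
- "All robotic prostatectomies are being performed by one surgeon and all open prostatectomies are being performed by one other surgeon" (Abstract, Methods/design).
- "200 men per treatment arm (400 men in total) are being recruited after diagnosis and before treatment through a major public hospital outpatient clinic" (Abstract, Methods/design). Recruitment was therefore still open when the block size was published.

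No blinding and no variation of block size are described.

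**The concern.** The sentence gives one rule two purposes that conflict. Forcing five men per arm in every ten secures balance. It also means that once one arm has five men, the rest of the block is settled. Keeping the list in an independent database stops anyone from reading ahead. It does not stop anyone from counting back, if they know the block size and can see earlier allocations. Here the size is published, and the arm shows in which surgeon's list a man joins. Age band and IPSS band can be known at recruitment.

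What is at stake is selection bias. If someone who can foresee the next allocation hastens, delays or discourages enrolment accordingly, the arms may differ in prognosis at entry. Most quality-of-life outcomes are self-reported. Several hypotheses (1, 3 and 4) are of no difference or comparability, where a small bias counts for more than it does against a moderate effect.

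**Working it through.** **The plan's own figures.** For the allocation rule the article gives only a property (unpredictable), so there is no figure to reproduce. Its one reproducible figure is power: 70% of 200 leaves 140 per arm, and with d = 0.5 and alpha 0.05 (taken as two-sided) power is 98.7%. The stated figure of over 90% is met, and nothing below changes it.

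**Inputs from the article.** Block of 10 with b = 5 per arm; 400 men; 3 × 3 = 9 cells.

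**Assumptions.** Equal cells give 400/9 ≈ 44 men each. An uneven split (age 10/40/50%, IPSS 60/32/8%) was also tried. The observer always guesses the arm that is behind; ties count as one half.

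**Complete block, observer who knows the block boundaries and all earlier allocations in it**

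- Certain allocations: 2b/(b + 1) = 10/6 = 1.67 of 10, or 16.7%.
- Correct guesses: b + [4^b / C(2b, b) − 1]/2 = 5 + (1024/252 − 1)/2 = 6.53 of 10, or 65.3%, against 50% by chance.

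If blocks were not nested in strata, one running tally would give these figures.

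**Whole trial with blocks nested in nine cells (simulation)**

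| Rule | What the observer tracks | Guessed correctly | Known for certain |
|---|---|---|---|
| Fixed 10 | Every cell | about 64.5% | about 15% (0.15 × 400 = 60 men) |
| Fixed 10 | Overall total only | about 55% | – |
| Varied 6–14, sizes not disclosed | Every cell | about 64.5% | almost none |
| Big stick, limit 5 | Every cell | about 54% | about 8% |

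Equal and uneven cells gave the same fixed-10 figures to within rounding. The big-stick rule is a fair coin within each cell until the imbalance reaches 5, after which the next allocation is forced. Its limit equals the largest imbalance possible in a block of 10.

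**Comparison with shorter fixed blocks.** The same formulas give 33% certain and 71% guessed for blocks of 4, and 25% and 68% for blocks of 6. Ten is the less predictable choice among these.

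**Size of a possible bias.** Let δ be the difference in mean prognosis between men put forward when one arm is expected and men put forward when the other is. With a correct-guess rate p, the difference between arms is δ(2p − 1). The article gives no value for δ; 0.3 SD is assumed.

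- Every cell tracked and every guess acted on: 0.3 × (2 × 0.645 − 1) ≈ 0.09 SD.
- Only certain allocations acted on: 0.3 × 0.15 ≈ 0.045 SD.
- Overall total only, p ≈ 0.55: 0.3 × 0.10 = 0.03 SD.

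The result is proportional to δ, so half the assumed value halves each figure. Against the planning effect of 0.5 SD, the range 0.03 to 0.09 is 6% to 18%.

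**The case against.** The strongest reply is that the figures describe a determined observer whom the article never shows. He must know where each block starts, keep a log for each of nine cells, and be able to delay or divert men. Even then about 85% of allocations are not certain. Study integrity does not say who makes the same-day call or that anyone keeps such a log, and it separates the sequence from clinical and research staff. Ten is a long block by comparison with 4 or 6. Outcomes are measured before surgery and the model compares rates of change, so steering on measured baseline status is at least partly handled.

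All of this stands as a limit on the size and likelihood of the problem. None of it supplies the property that the article claims, because separating the list from staff does not stop deduction from visible past allocations.

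Three stronger readings are tempting but unsupported:

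- A reader might infer that recruiters do foresee allocations and steer men. The article shows nobody tallying or timing consent.
- A reader might take the Background remark that in one case series "more than 94% of men had chosen robotic surgery" as evidence of manipulation here. It reports patient choice in a non-randomised series. Nothing shows that a man in this trial sees other men's allocations, so he could not time his own consent by them.
- A reader might infer that any resulting bias is beyond repair. Baseline adjustment can remove the part carried by measured covariates; the part carried by unmeasured prognosis would remain.

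**Conclusion.** The point holds in a conditional form. The stated rule does not have the stated property. With full tracking per cell, about 15–17% of allocations could be known and about 64–65% guessed; with only the overall total in view, about 55% could be guessed. The resulting selection bias would be about 0.03 to 0.09 SD. The upper end requires tracking of every cell and action on every guess, and the whole range rests on the assumed 0.3 SD. The share of men per cell, and the nesting of blocks within cells, are also assumptions. The point is worth acting on because the article itself supplies the conditions for the inference and the remedy is cheap. It does not discredit the men already randomised.

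**What to change.** 1. For men still to be randomised, generate blocks of randomly varied size within each stratum, and do not disclose the sizes to clinic and recruiting staff. This removes almost all certain allocations. It does not lower the guess rate, which stays near 65%. Short blocks should be avoided: sizes of 4, 6 and 8 raise the rate to about 68%.
2. If a lower guess rate is also wanted, a big-stick rule with limit 5 within strata is an option (about 54% guessed, 8% certain). Choosing between the two is a trade-off: one leaves fewer certain allocations, the other fewer good guesses.
3. Replace the statement that fixed blocks of 10 ensure unpredictability. Say instead that blocking secures balance, that the list is held independently, and from what date block sizes were varied and withheld.

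**Cost.** A small change in the randomisation database, with the date of change recorded. Final arm sizes will be slightly unequal, but unfinished blocks in nine strata already cause this. The simulated average absolute difference is about 3.1 men with fixed blocks of 10 and 3.2 with sizes of 8, 10 and 12. Under the big stick the SD of the total difference is about 9 men in 400. A difference of 9 costs (9/400)² ≈ 0.05% in efficiency.
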